### Intervention

One hundred participants will be recruited from Wuxi Central Rehabilitation Hospital over 3 years and randomly allocated into four groups. All groups will receive a total of 60 min of training per session to ensure comparable intervention intensity. Conventional occupational therapy will consist of 20 min of therapist-guided training followed by 40 min of supervised self-directed practice. Group A (UL-RAT + BFRT) will receive 20 min of UL-RAT combined with BFRT (Figure 2), followed by 40 min of conventional occupational therapy. Group B (UL-RAT + sham BFRT) will receive 20 min of UL-RAT with sham BFRT and 40 min of occupational therapy. Group C will receive 60 min of occupational therapy, during which BFRT will be applied during the therapist-guided training period. Group D will receive 60 min of conventional occupational therapy alone. All interventions will be administered once daily, 5 days per week, for a total duration of 4 weeks. Perceived exertion will be continuously monitored using the Borg Rating of Perceived Exertion (RPE) scale (6–20 points) (33), which has been shown to correlate well with physiological indicators such as heart rate. Training intensity will be adjusted to maintain RPE within a moderate range (≤13 points) (34).

**Figure 2 fig2:**
[figure not shown]
Illustration of robot-assisted training combined with blood flow restriction training.

The upper limb rehabilitation robot (Nanjing ESTUN Company) will be used in this study is a three-dimensional end-effector device designed to facilitate shoulder flexion and elbow flexion-extension movements (35). Before each session, the therapist will adjust the device height to accommodate the participant’s seated position, place the participant’s forearm securely in the designated slot, ensure neutral wrist alignment, and confirm a secure handle grip. All participants will perform active exercises with individualized weight compensation determined at baseline and adjusted as necessary based on performance. Task difficulty and assistance levels will be progressively modified according to predetermined criteria, including task completion rates and movement quality, to ensure appropriate training intensity. Participants will engage in four 5-min game-based tasks selected from standardized interactive options (e.g., fruit fight, airplane fight, basketball shooting, mosquito fighting, and ocean exploration), based on their preferences. The total active training duration will be 20 min.

Blood flow restriction will be applied using a B STRONG BFR training band (Park City, UT, United States) positioned at the proximal third of the upper arm. Before each session, limb occlusion pressure will be measured with a vascular Doppler device (VD-30 series, Hadeco, Japan). Training pressure will be set at 40% of arterial occlusion pressure to ensure participant safety (36), especially considering potential vascular impairment following stroke (37, 38). BFRT will be continuously applied throughout each training session without pressure adjustments between sessions. Participants will be closely monitored throughout each session for adverse signs such as excessive pain, numbness, abnormal skin coloration, or discomfort. Cuffs will be deflated immediately after each session to allow complete reperfusion.

Conventional occupational therapy aims to improve upper limb motor function through a structured and standardized program. Sessions will last 60 min each day, comprising 20 min of individualized therapist-guided training followed by 40 min of supervised self-directed practice. Therapy will include passive and active range-of-motion exercises (e.g., roller and plate exercises), fine motor training (e.g., gripping, releasing, finger opposition), and functional task-oriented training for activities of daily living (e.g., drinking water, grasping small objects, twisting bottle caps, stacking blocks, completing jigsaw puzzles). Progressive resistance training using equipment such as sandbags and dumbbells will be incorporated to enhance upper limb strength. All occupational therapy sessions will adhere to a standardized protocol. Although individual adjustments based on each participant’s functional status will be permitted, the overall structure, duration, and therapeutic components will remain consistent. Therapists will receive training prior to the study to ensure uniform intervention delivery.

### Outcomes

The primary outcome will be the FMA-UL motor assessment, a validated and reliable scale for evaluating upper limb motor function in patients during the subacute stroke phase (39). Only the upper limb section will be assessed, with scores ranging from 0 to 66; lower scores represent greater impairment.

Upper limb muscle strength will be assessed using a MicroFET2 handheld dynamometer (Hoggan Industries, Inc., West Jordan, UT, United States) (40). Maximum isometric strength will be measured in 13 muscle groups: anterior, middle, and posterior deltoids; latissimus dorsi; subscapularis; infraspinatus and teres minor; pectoralis major; middle trapezius; rhomboids; triceps; biceps and brachialis; and brachioradialis extensor carpi radialis longus. Each assessment will begin with an explanation and demonstration of movements, safety instructions, and testing procedures, followed by a brief warm-up to prevent muscle strain or fatigue. Strength will be tested using three maximum voluntary contractions per muscle group on both sides, with the average of the three trials recorded as the final value. Measurements will begin with the affected side, followed by at least a 30-s rest before assessing the unaffected side. Participants will be instructed to sustain each contraction for 5 s, aiming for maximum force within the first 3 s.

Surface electromyography (sEMG) will be recorded using a wireless BTS FREEEMG 300 system (41) (BTS Bioengineering, Milan, Italy). Prior to electrode placement, the skin will be prepared by shaving (if necessary) and cleaned with alcohol to reduce impedance. A pair of silver-silver chloride electrodes will be placed over the muscle belly, aligned with muscle fibers and spaced 2 cm apart. The muscles assessed will include the biceps brachii, triceps brachii, deltoid, and wrist extensor muscles. Participants will perform maximal voluntary isometric contractions lasting 7 s each, repeated three times per muscle. The sEMG signals will be sampled at 1,000 Hz and band-pass filtered between 20 and 500 Hz. Data will be recorded for offline analysis using BTS EMG-Analyzer software.

Grip strength will be assessed using a Jamar handheld grip dynamometer (United States) (42). Participants will sit with elbows flexed at 90 degrees and upper arms held close to the body. They will perform maximal isometric contractions by squeezing the dynamometer for at least 5 s. Each hand will be tested three times, with a one-minute rest interval between trials. The highest recorded value will be reported as the final result.

The Motricity Index (MI), which evaluates muscle strength in stroke patients, will also be used (43). The upper limb section includes muscle strength grading for three movements: pinching, elbow flexion, and shoulder abduction. The total MI score, ranging from 0 to 100, is calculated as the sum of the three movement scores plus one; higher scores indicate better muscle strength.

The Action Research Arm Test (ARAT) will evaluate upper limb dysfunction following stroke (44). It consists of 19 items across four movement categories: grasping, gripping, pinching, and gross movements. Performance will be rated on a 4-point scale (0–3), yielding a total possible score of 0–57; higher scores indicate better upper limb function.

The MBI will measure participants’ abilities in activities of daily living (45). It consists of 10 items, with total scores ranging from 0 to 100; higher scores represent greater functional independence.

### Statistical analysis

Statistical analyses will be performed using SPSS version 22.0 (IBM Corp., Armonk, NY, United States). All analyses will follow the intention-to-treat principle. Baseline characteristics will be summarized using means ± standard deviations or median (interquartile ranges) for continuous variables, and frequencies (percentages) for categorical variables. Baseline group differences will be assessed using one-way analysis of variance, Kruskal–Wallis tests, or chi-square tests, as appropriate. A two-factor repeated-measures analysis of variance (group × time) will examine changes over time and group differences, provided assumptions are met. If normality or sphericity assumptions are violated, linear mixed-effects models will be applied. The primary analysis will focus on the between-group difference in change from baseline between the UL-RAT + BFR group and the UL-RAT group. Comparisons involving BFR and control groups will be exploratory. *Post hoc* pairwise comparisons with appropriate adjustments will be conducted when significant interactions or main effects are identified. A two-sided *p*-value < 0.05 will indicate statistical significance.

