### Sample size estimate

Sample size was determined based on the primary comparison between the UL-RAT + BFRT group and the UL-RAT group. A minimal clinically important difference of 9 points on the Fugl-Meyer Assessment of the Upper Limb (FMA-UL) was adopted, which has been estimated for subacute stroke patients using anchor-based methods with the modified Rankin Scale (31). A standard deviation of 10 points was assumed, consistent with previous studies reporting FMA-UE scores in stroke populations (32). Using a two-sample t-test with a two-sided *α* of 0.05 and 80% power, the required sample size was calculated as 20 participants per group (G*Power 3.1.9.7). Although four parallel groups (UL-RAT + BFRT, UL-RAT, BFRT, and control) are included, additional groups primarily serve exploratory purposes. Assuming a 20% dropout rate, the total sample size was increased to 100 participants, resulting in 25 participants in each group.

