### Participant timeline

The schedule of enrollment, interventions, and assessments is presented in Figure 3. The FMA-UL, MI-UL, ARAT, and MBI will be assessed at three time points: baseline (pre-intervention), immediately after intervention completion, and at a 4-week follow-up. Muscle strength, surface electromyography, and grip strength will be assessed only at baseline and immediately post-intervention. In addition, pre-enrollment screening procedures (eligibility confirmation, informed consent) occur before baseline and are not part of the formal outcome assessment.

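### The default repeated-measures ANOVA drops anyone with a missed FMA-UL visit, which does not fit the intention-to-treat promise; the mixed model that would keep them is tied to an unrelated trigger

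*Protocol article*

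**What the plan says.** The Statistical analysis section sets the principle: "All analyses will follow the intention-to-treat principle". It names the software ("Statistical analyses will be performed using SPSS version 22.0") and the default model: "A two-factor repeated-measures analysis of variance (group × time) will examine changes over time and group differences, provided assumptions are met". The alternative model has one trigger: "If normality or sphericity assumptions are violated, linear mixed-effects models will be applied". The primary contrast is given without a visit: "The primary analysis will focus on the between-group difference in change from baseline between the UL-RAT + BFR group and the UL-RAT group".

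The Participant timeline section says: "The FMA-UL, MI-UL, ARAT, and MBI will be assessed at three time points". These are baseline, immediately after the intervention, and a 4-week follow-up. The Sample size estimate section plans for loss: "Assuming a 20% dropout rate, the total sample size was increased to 100 participants, resulting in 25 participants in each group". The article states no imputation or other rule for missing outcome values.

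**The concern.** A classical group × time repeated-measures ANOVA needs a complete row of visits for each participant and deletes incomplete rows. Once a visit is missed, the analysed set is the completers, whatever principle is declared. A participant who attends baseline and post-intervention but not the follow-up also leaves the post-intervention comparison, although the score needed for it was observed.

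The plan already names a model that would keep such participants, but links it to the wrong condition. If the assumption checks pass, the completer model stands however many visits are missing. The trigger is also only half apt. A mixed model is a legitimate response to failed sphericity. It does not remedy non-normality, because a linear mixed model assumes normal residuals too. As written, an assumption check on the trial data decides both the primary model and who is analysed.

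At stake are observed primary-outcome data and, under some patterns of loss, the validity of the comparison of UL-RAT + BFRT (arm A) with UL-RAT + sham BFRT (arm B).

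**Working it through.** **Inputs from the protocol article.** Difference 9 points, SD 10, two-sided α 0.05, power 80%, 20 per group before dropout, 20% dropout, 25 per group and 100 in total (Sample size estimate); three FMA-UL visits (Participant timeline).

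**1. The plan's own figure.** The normal approximation is n = 2(z₀.₉₇₅ + z₀.₈₀)² / (9/10)² = 2(1.960 + 0.842)² / 0.81 = 19.4, rounded up to 20 per group. Dropout: 20 / (1 − 0.20) = 25 per group, and 4 × 25 = 100. The stated figures reproduce. The exact noncentral-t calculation gives 79.2% power at 20 per group and 81.2% at 21, a trivial difference.

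**2. Who is left.** If all the 20% loss is missed assessments, 0.20 × 25 = 5 per arm are deleted. The primary comparison keeps 40 of 50, and the four arms together keep 80 of 100.

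**3. Power.** Exact t power at d = 0.9:

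| Analysed per arm | Power |
|---|---|
| 20 (all 20% deleted) | 79.2% |
| 22.5 (assumption: half of the loss misses only the follow-up and is kept for the post-intervention contrast) | 83.9% |
| 25 (complete data, a ceiling) | 87.7% |

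The first row is the planned size, so deletion causes no shortfall against the design. It only gives up information that was collected.

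**4. Bias, by simulation.** The following are assumptions, not figures from the article: SD 10 at each visit, equal correlation between visits, true difference 9.0 in change to post-intervention, 400,000 per arm, 20% loss in each arm. Gain-dependent loss means a logit slope of −0.1 per point of gain. Where loss depends on gain in arm A only, loss in arm B is random.

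| Pattern of loss (correlation 0.7) | Completers | Likelihood-based |
|---|---|---|
| Only the follow-up missed, gain-dependent in arm A only | 10.1 | 9.0 |
| Only the follow-up missed, gain-dependent in both arms | 9.0 | 9.0 |
| Post-intervention also missed, gain-dependent in arm A only | 10.1 | about 9.9 |

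At correlation 0.5, the first row gives about 10.7 to 10.8 for completers and 9.0 for the likelihood-based estimate.

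Further runs at correlations 0.5 to 0.7 used unequal loss of about 30% in arm A and 10% in arm B. Completers gave 7.5 to 8.1 when low baseline scorers were lost, and 10.2 to 10.6 when a poor post-intervention change led to a missed follow-up. The likelihood-based estimate stayed near 9.0. With 20% loss completely at random, both estimates stayed near 9.0.

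Bias can therefore go either way or be absent. The mixed model removes it when loss depends on observed scores. It removes little when the post-intervention score itself is missing for reasons tied to its value.

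**The case against.** **The article may simply be silent.** It gives no completers-only rule, and imputation before the ANOVA, set out in an analysis plan not shown, would avoid the deletion. This stands as a limit on the claim. It does not rescue the switch, which the article does state and which ties the better model to a condition unrelated to missing data.

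**A missed follow-up matters only if all three visits enter one model.** The primary contrast names no visit, the sample size rests on a two-sample t-test, and the abstract lists only baseline and post-intervention. This is fair. However, the Study design and Participant timeline sections list three visits, and sphericity is an issue only with three or more levels, so a three-visit model is the natural reading.

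**The 20% is a planning figure.** Participants who stop training but are still assessed are not deleted. This stands.

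**A reader might infer that the primary result will be biased because cuff discomfort drives people out of arm A and not out of the sham arm.** The documents do not support this. They do not describe the sham cuff or its pressure, so a difference in discomfort is conjecture. The cuff is worn only during the four training weeks, so people leaving for that reason would probably miss the post-intervention visit too. In that case the mixed model alone removes little of the bias (about 9.9 against 10.1).

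**A reader might also infer that the trial is underpowered.** It is not, on this ground: the inflation to 25 per arm is meant to leave 20.

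**Analysts are blinded, and the trial calls its efficacy aim preliminary.** Both lower the urgency. Neither makes the default model fit the stated principle.

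**Conclusion.** The point holds in a limited form. With no imputation stated, the default model and the intention-to-treat promise cannot both be kept once an FMA-UL visit is missed, and the mixed-model trigger does not address this. The size is about 10 of 50 participants in the primary comparison, if the full 20% loss is missed assessments and all three visits are modelled together.

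Bias is conditional on outcome- or prognosis-related loss that differs between the arms. The shift from 9.0 to about 10.1 illustrates one assumed pattern and is not a prediction. The power cost is secondary. This should be fixed, but it does not by itself invalidate the trial.

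**What to change.** Make a likelihood-based linear mixed model the primary analysis, whatever the assumption checks show. It should have group, visit and group × visit, an unstructured covariance, and all available FMA-UL values from all randomised participants. Define the primary contrast as the A versus B difference in change from baseline at one named visit. Delete the condition that assumptions be met and the switch that follows it. Keep the completer ANOVA at most as a sensitivity analysis.

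Add a missing-data sensitivity analysis that allows for outcome-related loss, because the mixed model does not remove bias when the post-intervention score itself is missing for such reasons.

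The cost is wording in the Statistical analysis section and one extra analysis. The mixed model is already named in the plan, and no participants or visits are added. The change should be made before outcome data are examined.

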### Randomization and blinding

An independent researcher not involved in recruitment, intervention delivery, or outcome assessment generated a simple random allocation sequence via computer-based randomization at a 1:1:1:1 ratio. Group assignments were sealed in opaque, sequentially numbered envelopes prepared prior to the study and securely stored by the same researcher. After participants completed baseline assessments and eligibility was confirmed, a research assistant uninvolved in intervention or assessments opened the next sequential envelope privately and disclosed the assigned group on a sealed note to the therapist before the initial intervention session. Outcome assessors and data analysts will remain blinded to group allocation throughout data collection and analysis. Due to the nature of robot-assisted upper limb interventions, blinding of treating therapists is not possible.

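### The primary comparison is in effect a raw change-score contrast; prespecifying baseline FMA-UL as a covariate would usually be more precise and would guard against chance baseline imbalance

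*Protocol article*

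**What the plan says.** The Statistical analysis section of the protocol article fixes both the primary contrast and the model. On the contrast: "The primary analysis will focus on the between-group difference in change from baseline between the UL-RAT + BFR group and the UL-RAT group". On the model: "A two-factor repeated-measures analysis of variance (group × time) will examine changes over time and group differences, provided assumptions are met". The fallback is "If normality or sphericity assumptions are violated, linear mixed-effects models will be applied", with no statement of how that model would treat the baseline value. No covariate is named for any of these. Baseline is dealt with only by testing: "Baseline group differences will be assessed using one-way analysis of variance, Kruskal–Wallis tests, or chi-square tests, as appropriate". No adjustment follows from those tests.

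The Randomization and blinding section says that an independent researcher "generated a simple random allocation sequence via computer-based randomization at a 1:1:1:1 ratio"; it mentions no stratification. Allocation is disclosed "After participants completed baseline assessments and eligibility was confirmed", so baseline FMA-UL is a pre-randomisation measurement available for everyone randomised. The Participant timeline section schedules FMA-UL at baseline, at the end of treatment and at the 4-week follow-up.

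The Sample size estimate section uses a two-sample t-test for the same comparison, with a difference of 9 FMA-UL points. On variability it says: "A standard deviation of 10 points was assumed, consistent with previous studies reporting FMA-UE scores in stroke populations".

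**The concern.** When baseline is one of the time levels, the group × time contrast between baseline and a later visit is the difference between arms in mean raw change. This forces the slope of the later score on baseline to be 1. With equal SDs at both visits the true slope is ρ, so the forced slope is too steep whenever ρ is below 1. Two things follow.

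- **Precision.** The change score carries baseline noise that a fitted slope would take out.
- **Imbalance.** If one arm happens to start higher, the change score over-corrects and the estimate moves against that arm. With simple randomisation and about 20 completers per arm, imbalances of a few points are to be expected.

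A further question is whether the sample-size calculation matches the analysis. A t-test with SD 10 fits a change-score analysis only if 10 is the SD of change. The wording points to an SD of scores, and the two differ unless ρ = 0.5.

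**Working it through.** **Inputs.** From the Sample size estimate section: difference 9, SD s = 10, two-sided α = 0.05, power 80%, 20 per group, 20% dropout, 25 per group, 100 in total. The correlation ρ between baseline and post-treatment FMA-UL is not given, so it is varied as an assumption. Equal SDs at both visits are also assumed.

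**The plan's own figure.** n = 2 × [10 × (1.960 + 0.842) / 9]² = 19.38, rounded up to 20 per group. Then 20 / 0.8 = 25 and 4 × 25 = 100. The stated figures reproduce. The exact noncentral-t power is 79.2% at 20 per group and 81.2% at 21, so 20 is right to within rounding.

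**Formulas.**
- SD of change = s√(2(1−ρ)).
- Residual SD under ANCOVA = s√(1−ρ²).
- Large-sample variance ratio, ANCOVA to change = (1−ρ²) / (2(1−ρ)) = (1+ρ)/2.
- Cost of estimating the slope with n per arm: multiply the ANCOVA variance by 1 + 1/(2n−4). At n = 20 this is 1 + 1/36 = 1.028.

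**Results at 20 completers per arm, taking 10 as the SD of scores.** Power is for a two-arm comparison at one post-baseline visit. The ANCOVA column includes the slope cost and one lost degree of freedom.

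| ρ | SD change | SD ANCOVA | (1+ρ)/2 | ratio × 1.028 | power, change | power, ANCOVA |
|---|---|---|---|---|---|---|
| 0 | 14.14 | 10.00 | 0.50 | 0.514 | 50% | 78% |
| 0.3 | 11.83 | 9.54 | 0.65 | 0.668 | 65% | 82% |
| 0.5 | 10.00 | 8.66 | 0.75 | 0.771 | 79% | 88% |
| 0.7 | 7.75 | 7.14 | 0.85 | 0.874 | 95% | 97% |
| 0.8 | 6.32 | 6.00 | 0.90 | 0.925 | 99.2% | 99.5% |
| 0.9 | 4.47 | 4.36 | 0.95 | 0.976 | about 100% | about 100% |

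The n per arm needed for 80% power (normal approximation), change versus ANCOVA, is 28 versus 18 at ρ = 0.3, 20 versus 15 at 0.5 and 12 versus 10 at 0.7.

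**Where the gain ends.** Setting (1+ρ)/2 × 37/36 = 1 gives ρ = 72/37 − 1 = 0.946. Simulation (40,000 trials per setting, 20 per arm) agrees: variance ratios are 0.67, 0.77, 0.87 and 0.98 at ρ = 0.3, 0.5, 0.7 and 0.9, then 1.005 at 0.95 and 1.015 at 0.98.

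**Chance imbalance.** With a score SD of 10, the standard error of the baseline difference between the two arms is 10√(2/20) = 3.2 points at 20 per arm and 10√(2/25) = 2.8 at 25. A 4-point imbalance is 4/3.16 = 1.26 standard errors at 20 per arm, which chance alone reaches in one direction or the other about one time in five. Given an imbalance d, the change-score estimate shifts by −(1−ρ)d. For d = 4 this is 2.8, 2.0, 1.2 and 0.4 points at ρ = 0.3, 0.5, 0.7 and 0.9, against a target difference of 9. In the simulation the correlation between the estimate and the baseline difference ran from −0.59 (ρ = 0.3) to −0.10 (ρ = 0.98) for change scores, and was about 0 for ANCOVA.

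**If 10 is instead the SD of change.** Calculation and analysis then agree, with 79.2% power at 20 per arm. The variance ratio (1+ρ)/2 does not depend on which SD is meant, so adjustment would still usually gain precision.

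**The case against.** The strongest reply is that the change-score analysis is valid: randomisation makes it unbiased, and where ρ is high it loses almost nothing. That stands. At ρ = 0.8 both analyses exceed 99% power, and nothing in the document favours 0.3 over 0.8. This is a matter of efficiency and robustness.

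A second reply is that the article is condensed, that covariates are often left to the analysis plan, and that the mixed model could treat baseline in a way close to ANCOVA (a constrained common baseline, for instance). In part this stands: the word unadjusted does not appear, and a change score analysed with a baseline covariate gives the same treatment estimate as ANCOVA on the later score. But the article itself fixes the contrast and the model, names no covariate, and keeps the mixed model as a fallback with baseline handling unstated. An analysis plan that added the covariate would be changing or extending this text.

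A reader might infer several stronger claims that do not hold:
- *Adjustment is always at least as precise.* True in large samples, but at 20 per arm it is slightly worse from ρ of about 0.95.
- *The planned power holds only at ρ = 0.5.* It is about 79% or more for every ρ from 0.5 upwards.
- *ANCOVA keeps 80% at any correlation.* It gives 78.0% at ρ = 0 and 79.7% at 0.2.
- *Adjustment removes baseline imbalance.* It removes only the part linearly related to outcome, and only for the covariate used.
- *The sample size is wrong.* The text does not settle whether 10 is the SD of scores or of change, so neither a shortfall nor a conservative margin can be declared.

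The power figures also simplify the plan: two arms and one post-baseline visit, where the stated model has four groups and three FMA-UL visits.

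**Conclusion.** The point holds as a worthwhile and nearly free improvement to a stated method. The primary contrast as written compares raw change scores although a complete pre-randomisation baseline is available. Adjustment would cut the variance by about (1−ρ)/2 in large samples: 35%, 25%, 15% and 5% at ρ = 0.3, 0.5, 0.7 and 0.9, and slightly less at 20 per arm. It would also take out conditional shifts of 1 to 3 points for a 4-point imbalance at ρ from 0.7 down to 0.3.

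The power shortfall is conditional on two things the document does not give: that 10 is the SD of scores, and that ρ is below about 0.5. If both hold, the planned analysis misses its stated power (65% at ρ = 0.3) while ANCOVA stays near or above it. Otherwise the gain is in precision and in protection against imbalance only.

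**What to change.** In the Statistical analysis section, prespecify baseline FMA-UL as a covariate in the primary comparison of UL-RAT + BFRT with UL-RAT. Either of these would do:
- ANCOVA of the post-baseline FMA-UL score on group and baseline FMA-UL; or
- a mixed model on the post-baseline visits, with group, visit, group × visit, baseline FMA-UL and baseline × visit.

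Include the covariate whatever the baseline significance tests show. Treat the other outcomes measured at baseline (strength, sEMG, grip, MI, ARAT, MBI) in the same way, each with its own baseline value.

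In the Sample size estimate section, state whether the SD of 10 refers to scores or to change, so that the calculation matches the analysis. If it refers to scores, give the assumed ρ or a range.

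The cost is wording only: the data are already collected, and neither the sample size nor the visit schedule changes. The amendment should be made before any unblinding.

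### The trial is powered on a plain A versus B test at 0.05, but the analysis section gives that contrast no test of its own and does not exempt it from the post hoc adjustment

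*Protocol article*

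**What the plan says.** The Sample size estimate section is explicit about what was powered: "Sample size was determined based on the primary comparison between the UL-RAT + BFRT group and the UL-RAT group". The difference is 9 points on the FMA-UL and the assumed SD is 10. The calculation is described as "Using a two-sample t-test with a two-sided *α* of 0.05 and 80% power", giving 20 per group, raised to 25 per group (100 in total) for 20% dropout. The other two arms are said to serve mainly exploratory purposes.

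The Statistical analysis section names one model, a four-group by time repeated-measures ANOVA, with a linear mixed model if assumptions fail. It then says: "The primary analysis will focus on the between-group difference in change from baseline between the UL-RAT + BFR group and the UL-RAT group". Comparisons involving the BFRT arm (C) and the control arm (D) are called exploratory. The next sentence contains the only pairwise tests the section describes: post hoc "pairwise comparisons with appropriate adjustments will be conducted when significant interactions or main effects are identified". The section closes with a two-sided 0.05 threshold. It names neither the adjustment nor the number of pairs it covers, and it does not say whether A versus B falls inside or outside this rule.

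**The concern.** The test used for sizing and the tests described for analysis are different. In a four-group ANOVA, A versus B is one of six pairwise comparisons. A reader who looks in the analysis section for the test that decides the primary question finds only a pairwise procedure that is conditional on an omnibus result and adjusted by an unnamed method. The sentence naming A versus B as the focus of the primary analysis fixes the contrast, but not the test, its level or its independence from the omnibus result.

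At stake is the conclusion on the trial's only powered comparison. Suppose the unadjusted p-value for A versus B is 0.02. Tested as a single contrast, it is significant. Under Bonferroni it becomes 3 × 0.02 = 0.06 for three pairs or 6 × 0.02 = 0.12 for six, and is not. Two analysts could each claim to follow the section and report opposite answers.

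The gate also fits the question poorly. It opens on any significant interaction or main effect, so a time effect is enough. General recovery is likely in patients enrolled within 6 months of stroke, so a time effect can be expected even without any treatment effect.

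**Working it through.** **Inputs from the Sample size estimate section.** Difference 9, SD 10, two-sided alpha 0.05, power 80%, 20 per group, 25 per group after dropout.

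**Assumption.** The primary contrast is a difference in change from baseline, but the SD of 10 is described as that of scores. I take 10 as the SD of change, which corresponds to a baseline-to-post correlation r of 0.5, and vary it in step 4.

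**1. The plan's own figure.** By the normal approximation, n = 2 × (1.960 + 0.842)² × (10/9)² = 2 × 7.85 × 1.235 = 19.4, so 20 per group. Dropout: 20/0.8 = 25 per group, 100 in total. The stated figures reproduce. With the exact noncentral t (38 df), power at 20 per group is 79.2%.

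**2. The same contrast with and without adjustment.** The noncentrality is 9 / (10 × √(2/n)), which is 2.846 for n = 20 and 3.182 for n = 25. The error term is the residual pooled over four arms, with 4n − 4 df (76 and 96). The critical value is the t quantile at 1 − alpha/2, with alpha = 0.05 divided by the number of pairs.

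| Rule for A versus B | Critical t (n = 20) | Power, 20 per arm | Power, 25 per arm |
|---|---|---|---|
| Unadjusted | 1.992 | 80.2% | 88.3% |
| Bonferroni, 3 pairs | 2.448 | 65.5% | 77.0% |
| Bonferroni, 6 pairs | 2.709 | 55.7% | 68.6% |

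Tukey over four groups, after a significant omnibus test on change, gives about 56–59% with 20 per arm and 69–71% with 25. For 80% power with this error term, Bonferroni needs 27 completers per arm for three pairs and 31 for six. With 20% dropout that is 27/0.8, so 34 per arm, and 31/0.8, so 39 per arm.

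**3. The gate.** I simulated four arms of 20 at two visits, with SD 10, r = 0.5 and A 9 points above B, over several patterns for C and D.

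- *Gate as worded (any of interaction, group or time significant).* With a common gain of 3 points in all arms, it opened in at least 99.9% of runs and A versus B power at 0.05 stayed at about 80%. With no common gain, it opened in about 94–100% of runs and power was about 79–81%.
- *Gate restricted to the group by time interaction.* Power was about 74% if only A differs, 72% with a half effect in C, 62–63% with half effects in both C and D, and 78–80% when C or D departs strongly.
- *No treatment effect in any arm, common gain of 5 points.* The worded gate still opened in about 99% of runs, so it screens out almost nothing.

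**4. Sensitivity to the SD of change.** If 10 is the SD of a single score, the SD of change is 10 × √(2(1 − r)). Power with 20 per arm and the pooled residual:

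| r | SD of change | Unadjusted | Bonferroni, 6 pairs |
|---|---|---|---|
| 0.3 | 11.83 | 66% | 39% |
| 0.5 | 10.00 | 80% | 56% |
| 0.6 | 8.94 | 88% | 68% |
| 0.7 | 7.75 | 95% | 83% |

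The documents do not give r.

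**The case against.** The strongest reply is that the analysis section already sets A versus B apart. It gives the contrast its own sentence as primary and calls comparisons with the other arms exploratory before it mentions post hoc tests. A declared primary contrast is not normally called post hoc, and the sample size section names the same pair with an unadjusted test. On that reading the gate and adjustment belong to the exploratory pairs and the 80% stands. This reading is reasonable. A reader might infer that A versus B is tested only as a gated, adjusted post hoc pair, but the text does not say so. It does not say the opposite either, and it supplies no other test for the contrast.

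A second reply is that the gate does no harm to power. This also stands. A reader might infer that an omnibus gate shared with two exploratory arms lowers the power markedly, and an interaction-only gate could. The wording admits any main effect, however, and under that rule the loss is negligible.

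A third reply is that Bonferroni over six pairs is an assumption, that an appropriate adjustment for one primary contrast may be none, and that the method may be left to an analysis plan. It is true that the documents do not fix the size of the loss. The point is not that the method is unnamed. It is that the stated rule, read literally, reaches a contrast that was sized without any adjustment.

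**Conclusion.** The point holds as an inconsistency between the sizing and the analysis text, not as a demonstrated loss of power. The sample size reproduces, and the primary pair is the same in both sections. What is missing is a test for that pair that matches the one used for sizing, and an express statement that the adjusted post hoc rule does not apply to it.

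If the adjustment is applied to A versus B, power with 20 completers per arm is about 65% (three pairs) or 55–56% (six pairs) instead of about 80%. With all 25 per arm retained it is about 77% or 68–69%. These figures assume a difference of 9, an SD of change of 10 and Bonferroni. With an SD of change near 7.75, even the six-pair version keeps 83% at 20 per arm; with a larger SD the loss is worse. The gate as worded adds almost nothing to the loss and offers almost no protection. It would matter only if narrowed to the interaction, where power would range from about 62% to about 80% depending on arms C and D.

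**What to change.** In the Statistical analysis section, state that A versus B in change in FMA-UL is a single pre-planned contrast from the four-arm model, reported with a 95% confidence interval and tested at two-sided 0.05 regardless of the omnibus results and without multiplicity adjustment. State that the omnibus test followed by adjusted pairwise comparisons applies only to the exploratory pairs. With the residual pooled over four arms (76 df), this contrast has about 80% power at 20 per arm under the plan's own assumptions, so the sample size section can stay as it is.

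If the adjustment is meant to cover A versus B, name the method and the number of pairs and restate the power for that test.

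The first option costs one or two sentences and needs no extra data or participants. The second would either lower the stated power or, on the assumptions above, raise the number needed per arm.
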